# Telemedicine home-based management in patients with chronic heart failure and diabetes type II: study protocol for a randomized controlled trial

**DOI:** 10.1186/s13063-024-08171-0

**Published:** 2024-05-21

**Keywords:** Heart failure, Diabetes mellitus type II, Tele-health, Telemedicine, Teleassistance, Telemonitoring, Telerehabilitation, 6-min walk test, Motivational feedback, Randomized controlled trial

## Abstract

**Background:**

Heart failure and type 2 diabetes are prevalent public health issues in Europe. These complex chronic conditions require extensive pharmacological management, ongoing self-care, and behavioral changes. Despite the known benefits of lifestyle changes, such as regular exercise and better control of blood sugar levels, patients may need help implementing the recommended changes. This study aims to assess the effectiveness of a telemedicine program for managing heart failure and type 2 diabetes at home. The program focuses on promoting lifestyle changes.

**Methods and analysis:**

During scheduled outpatient cardiology evaluations, eligible patients are recruited and randomly assigned to either an intervention or control group in a 1:1 ratio. The intervention group receives support from a nursing case manager through a structured home-based teleassistance program and a trainer for daily physical activity stimulation. They also have access to teleconsultations with cardiologists and diabetes specialists as needed, telemonitoring of vital signs, and daily step tracking. An app records and monitors daily drug treatment, glycemia, blood pressure, heart rate, and other clinical parameters. Patients can also self-report symptoms and communicate via a chat and videoconference system with a Nurse Case Manager. The control group receives routine care. Data collection occurs before intervention and 6 months after baseline during a new outpatient cardiology evaluation. The primary outcome is to measure the difference in the distance walked during a 6-min walk test between baseline and after 6 months. The key secondary outcomes include improving the disease status and physical activity profile. Data will be analyzed according to the intention-to-treat principles.

**Discussion:**

This study will provide evidence on the efficacy of a telemedicine home-based management model to maintain correct lifestyles in patients with both heart failure and type 2 diabetes, improving self-management, their empowerment on the diseases, and increasing their knowledge and ability to recognize symptoms early.

**Trial registration:**

ClinicalTrials.gov NCT05633784. Registered on November 30, 2022.

**Supplementary Information:**

The online version contains supplementary material available at 10.1186/s13063-024-08171-0.

## Background

As the population of industrialized countries ages, there is a significant rise in chronic diseases. Heart failure (HF) and type 2 diabetes (T2DM) are prevalent public health issues in Europe. HF affects 1–2% of adults and increases to over 10% in those aged 70 years or older [1, 2]. T2DM is continuously growing and is a particular concern in HF, where it is greater than 10% [3–6].

The weight of comorbidities is one of the main factors modifying the risk of hospitalization for HF [7, 8]. These complex chronic conditions require extensive pharmacological management, ongoing self-care, and behavioral changes (diet modification, sodium restriction, weight, and blood glucose monitoring). Adherence to recommendations regarding lifestyle modifications, such as increasing physical activity, is often limited despite the favorable effects these changes have on the chronically complex patient, as recommended by European and American guidelines [1, 2, 9, 10]. In patients with T2DM, more daily steps are associated with lower glycated hemoglobin (HbA1c) values and reduced waist circumference and body mass index [11, 12].

A complex drug regimen, typical of these diseases, is often associated with low adherence in patients with HF and T2DM, but it is an essential factor for improving health in patients with HF and DM [13]; on the contrary, patient adherence continues to be poor, leading to errors, adverse events, hospitalizations, and death [14, 15]. Therefore, interventions are needed to improve all these factors and optimize adherence.

Many programs try to change unhealthy lifestyles and help patients maintain a healthy life for as long as possible. In the Information and Communication Technology era, Telemedicine could be an alternative to promote healthy behaviors. A customized home telemedicine program founded on individual needs and risk profiles might be the best approach to plan the follow-up care of patients with complex chronic conditions. These programs should include routine self-management support, outcome measures, and electronic information systems to share patient data among the healthcare professionals engaged. These programs can provide tailored and scalable solutions for high-risk populations with multiple comorbidities, especially those with chronic illnesses, and promote continuity of care, allow for disease monitoring, prevent complications, and reduce disability [16, 17].

Patients with chronic and comorbid conditions require a comprehensive home care plan. Through our past experiences, we have found that telemedicine programs, which include teleassistance, telemonitoring, and teleconsultation, help these patients manage their conditions and take control of their health [18, 19].

Telemedicine can assist in recognizing symptoms early, managing medical devices and apps, identifying obstacles to adherence to therapy, such as adverse effects of drugs, checking if the intensity of physical therapy is adequate, and facilitating communication between professionals, such as nurses, physiotherapists, general practitioners, specialists, and pharmacists. This collaboration among healthcare providers is crucial for ensuring the best possible care for the patient and improving their overall awareness of their health status [18, 19]. Involving family members in the educational plan is essential for success and critical to the outpatient phase.

In this context, the nurse has a central role in improving the patient’s ability to increase self-management and empowerment and needs particular communication skills [20–22].

Furthermore, telemedicine applications, such as digital devices for recording and sending vital parameters and apps, can significantly change the quality of communication and the working methods of professionals [23].

Digital devices and mobile apps integrated into the treatment of chronic diseases can aid in the early diagnosis and treatment of potential disease instabilities. However, it is essential to consider how patients may react to the introduction of digital technology, as only some are technologically prepared. To ensure successful implementation, end-user guidance during the design and development is crucial [24].

The presence of a reference figure can assist patients in overcoming any apprehension they may have about using technology. Patients tend to be more receptive to technology when they believe it is crucial. All this can ultimately lead to a better patient experience and outcome [25].

The proposed trial (NET-2018–12367206-3) is part of the Italian Network Project “TELEMECHRON study” (NET-2018–12367206) [26] and intervenes to approach the solution of the medical-nursing and management problems that patients with chronic diseases face at home.

Our study aims to test the effectiveness and feasibility of an integrated, home-based medical/nursing intervention with trainer support for exercise versus conventional care in patients with CHF and T2DM. This paper aims to describe the trial’s design and rationale.

## Methods/design

### Study design and setting

This study (ClinicalTrials.gov ID: NCT05633784) is a consecutive, multicenter, open, randomized controlled trial. All patients are enrolled during the scheduled outpatient disease control visit (T0) and seen again in the outpatient department after 6 months (T6).

The study strategy is registered, constructed, and presented according to the recommendations for Interventional Trials (SPIRIT) [27] (SPIRIT checklist, Additional file 1) and Consolidated Standards of Reporting Trials (CONSORT) guidelines [28].

Figure 1 shows the flow chart of the study design.

**Fig. 1 Fig1:**
[figure not shown]
Flow chart of the study design

### Study sites and patient population

Patients are recruited from the Cardiology Departments of three hospitals in the Lombardy Region, Italy (Istituti Clinici Scientifici Maugeri IRCCS, Institute of Lumezzane, Brescia; Bolognini Hospital, Seriate, Bergamo; Papa Giovanni XXIII Hospital, Bergamo).

### Eligibility criteria

The inclusion criteria are as follows:Patients aged ≥ 18 yearsA documented diagnosis of HF (HF with reduced or preserved ejection fraction) without hospitalization due to decompensated HF in the last 3 monthsDiagnosis of T2DM in treatment with antidiabetic drugsAbility to walk without aidsWritten informed consentConsent to the use of devices and app

The exclusion criteria are as follows:The new-onset HF diagnosisLife expectancy of less than 6 monthsMedical issues that preclude participation in the programPhysical activity limitationImpossibility of using mobile technology

### Randomization

Patients are screened in the outpatient departments of the three hospitals during routine HF visits. A Nurse Case Manager reviews the scheduled office visits and personal electronic records weekly to identify patients eligible for the study. The study physician verifies their eligibility based on the inclusion criteria during the office visit and screens any other patients. All eligible patients are asked to participate, and those who give their consent are randomized (1:1) into either the intervention (IG) or control group (CG). Patients are allocated using a computer-generated table in fixed blocks of four, with the allocation sequence concealed from investigators to prevent selection bias. A separate randomization list is created for the three centers involved.

Due to the intervention’s nature, the patients and physicians know group allocation. However, outcome assessors and data analysts will be blinded to the allocation.

We have standardized the nursing approach as much as possible by conducting joint staff training, organizational meetings, and planning before patient enrolment in the three hospitals involved.

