#### Intervention program

Upon enrollment, the patients receive the tracker bracelet, the electrocardiograph device, and a smartphone with pre-installed apps for receiving the respective information on wearable devices.

The Nurse Case Manager coordinates activity and promotes patient learning of disease self-management techniques to prevent exacerbations; she/he plays a central role in all home care continuity interventions, becoming a key interface in the dialogue between patients and specialists.

The educational plan involves family members and is crucial to the program’s success.

An agenda of scheduled contacts is shared with the patient.

During the teleassistance program in the 6-month home-based study period, the nurse:Collects information regarding medical history and symptomsProvides health education and trainingVerifies prescription adherenceEvaluates general well-beingAssesses the level of assistance provided by the caregiverUpdates the computerized clinical fileActivates specialist intervention for a teleconsultation if necessary

Patients can contact their nurse during operating hours for clinical, symptom, or treatment-related issues.

Patients are encouraged to perform physical activity at least thrice a week, reinforcing the importance of lifestyle changes and exercise, asking them always to wear their Fitbit to monitor their daily steps constantly.

Furthermore, the patients are encouraged to update the “TreC Cardio” app information by entering any symptoms and biological parameters (blood pressure, heart rate, weight, blood sugar, etc.), viewable by the nurse on the web dashboard.

The healthcare personnel will be able to remotely manage the treatment path of the individual patients enrolled by prescribing therapies and tasks, view the progress of the clinical parameters collected and entered by the patient (e.g., vital signs, symptoms), interact with the patient through a chat for exchange of text messages and the sending of multimedia files by the patient, activate a videoconference, and deliver questionnaires.

The research team continuously monitors the data to ensure patients comply with the intervention. Patients are contacted if the nurse receives signs and symptoms of a worsening clinical condition to resolve problems with device malfunctions or in the event of failure to enter information into the app.

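### Fixed blocks of four per centre in an open trial allow up to one third of allocations to be deduced, so hiding the list does not fully conceal the sequence

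*Protocol article*

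**What the plan says.** All the relevant facts are in the protocol article.

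- **Sequence (Randomization).** Allocation is 1:1. "Patients are allocated using a computer-generated table in fixed blocks of four, with the allocation sequence concealed from investigators to prevent selection bias". Also: "A separate randomization list is created for the three centers involved".
- **Blinding (Randomization).** "Due to the intervention’s nature, the patients and physicians know group allocation". Outcome assessors and data analysts are to be blinded.
- **Who finds and admits patients (Randomization).** "A Nurse Case Manager reviews the scheduled office visits and personal electronic records weekly to identify patients eligible for the study". Then: "The study physician verifies their eligibility based on the inclusion criteria during the office visit and screens any other patients".
- **The nurse's other role (Intervention program).** "The Nurse Case Manager coordinates activity and promotes patient learning of disease self-management techniques to prevent exacerbations".
- **Entry criteria (Eligibility criteria).** Three exclusions call for judgement: medical problems that rule out the programme, limits on physical activity, and inability to use mobile technology.
- **Limits on choice.** The trial is described as consecutive (Study design and setting), and every eligible patient is to be invited (Randomization).
- **Timing.** The article appeared on 21 May 2024. Recruitment began in August 2022 and was due to end in September 2024 (Trial status).

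**The concern.** The plan offers concealment of the list as its protection against selection bias. That works only if the next assignment cannot be inferred from earlier ones. With a constant block of four, a list for each centre and open assignments, the fourth allocation in every block follows from the first three, and the third follows from the first two whenever those match. Keeping the list out of sight does not hide these.

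The people placed to use such knowledge are those who admit patients. The Nurse Case Manager identifies candidates and also coordinates the intervention, so this role sees both past assignments and coming candidates. The physician who verifies eligibility is unblinded and applies criteria that need judgement. The primary outcome is walking distance in the 6-minute walk test (6MWT), which depends on fitness and motivation, and both can be sensed at a clinic visit. If a doubtful patient is held back when control is due, or a keen one is entered when intervention is due, the arms differ before treatment starts. Blinded outcome assessors do not protect against that.

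**Working it through.** The article gives no predictability figure, so there is none to reproduce.

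**Inputs.** Block size 4, fixed, 1:1, so two per arm in each block (Randomization). Planned N = 240, SD = 115 m, 104 evaluable patients per group, target difference 45–50 m (Sample size). Assumed, because the article does not give them: an observer who knows the block size and follows every local assignment; the size of any selection effect; and a baseline-to-6-month correlation of 0.7.

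**1. Allocations known for certain.** There are 6 equally likely blocks. AABB and BBAA each contain 2 forced positions. ABAB, ABBA, BABA and BAAB each contain 1.
- Mean per block = (2×2 + 4×1)/6 = 4/3.
- Share = (4/3)/4 = 1/3 = 33.3%.
- By position: 0, 0, 1/3, 1.
- Of 240 patients: 240/3 = 80.

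**2. Best-guess rate (always guess the arm with more places left).**
- Position 1: 1/2.
- Position 2: 2/3.
- Position 3: 1/3×1 + 2/3×1/2 = 2/3.
- Position 4: 1.
- Mean = (1/2 + 2/3 + 2/3 + 1)/4 = 17/24 = 70.8%, against 50% by chance.

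**3. Illustrative effect on the primary comparison.** Suppose the analysed outcome is shifted by +s in predictable intervention slots and −s in predictable control slots. One third of each arm is affected, so bias = (1/3)×2×s.
- SE of a 6-month comparison = 115×√(2/104) = 15.9 m.
- SE of a comparison of change, r = 0.7: SD = 115×√(2×0.3) = 89.1 m, so SE = 89.1×√(2/104) = 12.4 m.
- Type I error = Φ(−1.96 + bias/SE) + Φ(−1.96 − bias/SE).

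| s (assumed) | bias | type I error, SE 15.9 | type I error, SE 12.4 |
|---|---|---|---|
| 5 m | 3.3 m | 5.5% | 5.8% |
| 10 m | 6.7 m | 7.0% | 8.4% |
| 15 m | 10 m | 9.6% | 12.8% |

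Each column takes s as a shift in the outcome that it analyses. A 15 m advantage in walking distance present equally at both visits would cancel from the change. If selection were on measured baseline distance with r = 0.7, the bias in change would be (1/3)×2×15×(0.7 − 1) = −3 m, against the intervention.

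**4. Alternative schemes.** The fixed-size values are exact. The varying-size values come from simulation of lists of 80 patients (240/3, assuming equal centres), with an observer who knows the set of sizes and updates after each assignment.

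| Scheme | Known for certain | Best guess |
|---|---|---|
| Fixed 4 | 33.3% | 70.8% |
| Fixed 6 | 25% | 68.3% |
| Fixed 8 | 20% | 66.6% |
| Random 4, 6 | 5.5% | 69.1% |
| Random 4, 6, 8 | 2.2% | 67.9% |

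**The case against.** **Tracking is not documented.** Nothing in the article says that site staff know the block size or follow the assignments. If they learned the size only from publication, and accrual was even over the 26 months, about 240×(4.3/26) ≈ 40 patients came afterwards, of whom about 40/3 ≈ 13 would be deducible. Whether sites knew the size earlier depends on the full protocol, which is not shown. This stands: 80 of 240 is a ceiling, not an estimate.

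**The recruitment rules limit selection.** Enrolment is consecutive at scheduled visits and every eligible patient is to be invited. Steering would mean breaking those rules or stretching an exclusion criterion. This narrows the risk, but does not cover judgement about who is eligible.

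**Analysis can deal with part of it.** The 6MWT is measured at baseline in all randomised patients, and the abstract defines the primary outcome as a change. Adjusting for baseline distance or analysing change largely handles selection on measured walking distance. A reader might infer that the bias cannot be removed in analysis; that holds only for unmeasured traits such as motivation.

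**Concealment is weakened, not destroyed.** A reader might infer that the claimed concealment is defeated altogether. Even for a perfect tracker, two thirds of allocations are not certain.

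**The release mechanism is not described.** The article does not say who releases the assignment or how. An article commonly leaves that to the full protocol, so it is no part of this point.

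**Conclusion.** The point holds as an avoidable weakness in a method that the article itself states. The design does not fully deliver the concealment it claims: in the worst case one third of allocations are certain and the best-guess rate is 71%. That arithmetic is exact, given an observer who knows the block size and follows all local assignments. The nurse's double role, the unblinded physician and the judgement-based exclusions make such use possible; the article gives no evidence that it happened.

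The consequence is much less certain than the predictability. A reader might take a type I error of 10–13% as the expected result. It is not: that range comes only from the upper end of an unsourced 5 to 15 m shift, and only if the shift falls on the analysed outcome itself. The full illustrative range is about 5.5% to 13%, with a bias of about 3 to 10 m against a target of 45–50 m.

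**What to change.** For all remaining randomisations, replace the three centre lists with new, centrally generated, centre-stratified lists whose block sizes vary at random, for example among 4, 6 and 8. Do not disclose the sizes to the sites or publish them until recruitment ends.

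The gain is that certainty is almost removed, from 33% of allocations to about 2%, even if staff learn the set of sizes. It should not be presented as making the sequence unguessable, since the best-guess rate falls only from 71% to about 68%.

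The cost is three new lists, a short amendment, and a possible arm imbalance of up to 4 within a centre instead of 2. The change helps only patients not yet randomised, so its value shrinks as the planned end of recruitment in September 2024 approaches. For those already randomised, a baseline-adjusted comparison of the 6MWT would leave mainly selection on unmeasured traits.

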#### Outcome assessments

##### Primary outcome measures

The primary outcome is exercise tolerance improvement measured by the difference in the meters walked at the 6MWT. The test measures the distance walked when subjects are asked to walk as fast as possible for 6 min, and performance in this test has been used to measure cardiovascular exercise capacity, particularly in patients with congestive heart failure [30] and diabetic patients [31].

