#### Sample size

Based on the literature analyzed [40, 41] of the experience developed over the years in patients with heart failure [42] and patients with a complex phenotype, SCC and COPD [19], followed by remote surveillance, we estimated a sample of 240 patients who could be evaluated to demonstrate efficacy on the primary outcome. The number should be sufficient to establish an anticipated difference of 45–50 m in walking distance at the 6MWT (primary endpoint) between the intervention and control group to demonstrate a statistically significant difference between groups applying a *t*-test with alpha = 0.80 and beta = 0.05. A mean of 360 m (SD = 115) was considered. We performed a comparison test between two independent means (unpaired data) with equal sd (sd1 = sd2 = sd) in the two groups. Therefore, assuming an SD = 115 and delta = 28,217, the sample is 208 patients, 104 per group. Thus, considering the 15% of patients not present at T6 for calculating the endpoint (dropout), the sample becomes 239.

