### Statistical analysis

Statistical analysis will be carried out by a certified health professional using STATA software (College Station, TX, USA). Data will be descriptively analyzed and presented as percentage or mean ± standard deviation for all clinical variables, median ± interquartile (IQ) range for variables without a normal distribution, and percentage for categorical and binary variables. The Kolmogorov–Smirnov test will test the distribution and normality of variables. To compare groups at T0, the Student *t*-test, the Mann–Whitney-Wilcoxon test for continuous variables, and the chi-squared test for categorical variables will be used.

Two-way analysis of variance (ANOVA) will analyze the effects of the intervention for repeated measures (time and group). A post hoc analysis will be conducted when the ANOVA *F* ratio is significant for the Student *t*-test among times and groups, and Bonferroni’s correction will be applied. Statistical significance is defined as *P* = 0.05.

Data will be primarily analyzed according to the intention-to-treat principle. An on-treatment analysis will be subsequently performed to assess whether protocol deviations have caused bias. Participants with documented deviation from the study protocol (i.e., patients in the intervention group who received only some of the intervention or participants in both groups with incomplete follow-up data) will be excluded.

No interim analysis is planned as no harm to patients is expected from this trial. There is no reason to stop prematurely other than the end of the financing.

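### Randomisation is stratified by centre but the stated analysis leaves centre out: a minor, conditional loss of precision, with no bias and no loss of the planned power

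*Protocol article*

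**What the plan says.** All references are to the protocol article.

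- **Randomization.** Of eligible patients, "those who give their consent are randomized (1:1) into either the intervention (IG) or control group (CG"). The method is given as "Patients are allocated using a computer-generated table in fixed blocks of four", and "A separate randomization list is created for the three centers involved". This is randomisation stratified by centre, with three strata.
- **Statistical analysis.** The outcome model is stated with its factors: "Two-way analysis of variance (ANOVA) will analyze the effects of the intervention for repeated measures (time and group"). The follow-up step is "A post hoc analysis will be conducted when the ANOVA *F* ratio is significant for the Student *t*-test among times and groups", with a Bonferroni correction. Baseline comparisons use t, Mann–Whitney–Wilcoxon and chi-squared tests. Centre is mentioned in none of these.
- **Primary outcome measures.** "The primary outcome is exercise tolerance improvement measured by the difference in the meters walked at the 6MWT". The abstract makes clear that the difference is between baseline and 6 months.
- **Sample size.** The calculation is an unpaired comparison of two means with a common SD of 115 m, giving 104 per group. It takes no credit for stratification.

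**The concern.** Under 1:1 allocation in blocks of four from a separate list per hospital, the arms can differ by at most two randomised patients in any centre. Between-centre variation therefore contributes almost nothing to the true sampling error of the arm difference. A test that leaves centre in the residual still counts that variation as noise. If centre is prognostic for the quantity tested, the reported standard error exceeds the true one, confidence intervals are wider than they need be, and the test rejects less often than its nominal level.

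The stake is precision and calibration. The estimate stays unbiased and the type I error is not inflated. The point concerns the article because it names the model's factors explicitly, and they do not match the design it describes.

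**Working it through.** **Inputs.** SD 115 m, difference 45 m (the lower end of the stated 45–50 m) and 104 per group come from Sample size. The error rates are printed as "alpha = 0.80 and beta = 0.05"; read as two-sided alpha 0.05 and power 0.80, they reproduce the stated number. Centre's share of variance, *c*, is not given and is **assumed** at 0 to 10%. The baseline-to-T6 correlation is not given and is **assumed** at 0.7.

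**Step 1: reproduce the plan's figure.** SE = 115 × √(2/104) = 15.95 m, and 45/15.95 = 2.82. The noncentral t calculation needs 104 per group (208 in all) and gives power 0.802; the normal approximation gives 103 per group. Then 208 × 1.15 = 239.2, the stated 239. The trial was thus sized for an unadjusted test on the full SD.

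**Step 2: between-arm comparison at T6.** Total SD is held at 115 m and the arms are balanced within centre.

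- Reported SE without centre: 15.95 m. True SE: 15.95 × √(1−c). Overstatement: 1/√(1−c).
- Actual type I error: 2[1 − Φ(1.96/√(1−c))].
- Power without centre: Φ((45 − 1.97 × 15.95)/(15.95√(1−c))).
- Power with centre: noncentral t with SD 115√(1−c) and 204 df.

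| c (assumed) | SE overstated by | Type I error without centre | Power without centre | Power with centre | Points forgone |
|---|---|---|---|---|---|
| 0% | 0% | 5.0% | 0.802 | 0.802 | 0 |
| 1% | 0.5% | 4.9% | 0.804 | 0.806 | 0.2 |
| 2% | 1.0% | 4.8% | 0.805 | 0.810 | 0.5 |
| 5% | 2.6% | 4.4% | 0.808 | 0.822 | 1.4 |
| 10% | 5.4% | 3.9% | 0.815 | 0.841 | 2.6 |

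A simulation (20,000 replicates, 208 patients) at c = 10% agrees: type I error 3.9% without centre and 5.1% with it; power 0.810 and 0.839.

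**Step 3: the time-by-group contrast.** With two time points this is the between-arm comparison of change, so a constant centre difference in level cancels. SD of change = 115 × √(2 × (1 − 0.7)) = 89.1 m, and SE = 89.1 × √(2/104) = 12.35 m. The simulation, with centre also explaining 10% of the variance in level, gave:

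| Centre share of the variance of change (assumed) | SE without / with centre (m) | Power at 30 m without / with centre |
|---|---|---|
| 0% | 12.34 / 12.34 | 0.68 / 0.68 |
| 2% | 12.34 / 12.21 | 0.68 / 0.68 |
| 5% | 12.34 / 12.03 | 0.68 / 0.70 |
| 10% | 12.34 / 11.70 | 0.68 / 0.72 |

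The 30 m difference is used only for illustration. At 45 m, power for this contrast is about 0.95 or more in every row, with or without centre.

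**The case against.** The strongest objections, and what remains of each:

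- **Planned power is not lost.** A reader might infer that power already paid for is being thrown away. Sample size does not support that. The number was set for an unadjusted comparison on the full SD, and in Step 2 the unadjusted power starts at 0.802 and rises with c. Only additional power is forgone. This objection stands.
- **The contrast that answers the primary question may be unaffected.** A reader might also infer that standard errors are too large for the primary and every secondary comparison. The primary outcome is change from baseline and the model is time by group, where stable centre differences drop out. A loss needs 6-month change itself to differ by centre. This stands for the interaction. It does not cover the group main effect or the post hoc between-arm t-test at T6, where differences in level do count.
- **Centre may not be prognostic.** No centre variance is reported, the sites are three cardiology departments in one region, and the nursing approach was standardised through joint training. This stands as a reason to start the assumed range at zero. It does not show that centre has no influence.
- **An analysis plan that is not shown may add centre.** That is possible, and nothing in the article rules it out. But the article states the model's factors instead of leaving them open, so the mismatch with its own randomisation can fairly be raised.

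**Conclusion.** The point holds in a limited form. The article stratifies by centre and then states an analysis that ignores the stratification. If centre is related to the outcome analysed, the effect runs one way: standard errors too large, tests conservative, precision forgone. There is no bias and no inflation of type I error, and at 208 evaluable patients with a total SD of 115 m the planned 80% is retained.

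The size depends on an assumption the documents cannot settle. Over the assumed 0 to 10% range the cost is small for a T6 comparison. For the time-by-group contrast it runs from nothing to about four points of power at 30 m, and the upper end requires centre to explain 10% of the variance of change at the assumed correlation of 0.7. Severity: minor. It is a free improvement and does not correct an invalid analysis.

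**What to change.** Add centre as a three-level fixed effect to the primary model and to the between-arm models for the continuous secondary outcomes. There are two ways to do so:

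- If the repeated-measures ANOVA is kept, include centre and **centre-by-time**. Centre as a level term alone does nothing for the time-by-group contrast.
- Otherwise, model T6 6MWT (or its change) on group, baseline 6MWT and centre. Baseline adjustment is a separate choice that this point does not require.

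The Statistical analysis section should say which is used. Hospitalisation for all causes should be considered separately: if it is analysed by logistic regression, adding centre changes the odds ratio from a marginal to a centre-conditional quantity.

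The cost is two degrees of freedom out of about 200, with no new data and no change to the sample size. The article reports that recruitment was still under way at submission, so the term can be specified before the analysis.
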